#### Randomization and masking

Patients will be enrolled in this trial by gastroenterologists, surgeons, oncologists, and endoscopists who will evaluate cases in the inpatient wards or outpatient consultation areas. Investigators of each center will be responsible for entering all necessary criteria to an online platform that will generate the randomization sequence, and participants will be randomized with an arbitrary number.

A code list will be generated by our biostatistics department, using R software (v 3.6.3) by randomization with a 1:1 randomization ratio, by blocks, stratified by age (< 65 years old/> 65 years old) and by the presence of liver metastases. The assumption is made that liver metastasis may elevate bilirubin and cholestasis parameters without involving bile duct obstruction. Everyone will be assigned a randomization code along with the treatment that corresponds to it. Once the patient meets the eligibility criteria and has provided informed consent, we will proceed to the allocation of each participant centrally, ensuring allocation concealment, and based on the randomization list. To prevent different subject recruitment rates at the various hospitals from interfering in the development of the study, the entire population will be randomized in blocks of four between the two treatment possibilities.

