#### Statistical analysis

Statistical analysis will be carried out with the R statistical software (version 3.6.2) supervised by the Biostatistics team of our research institute (IDIBELL).

Intention-to-treat and per-protocol analysis will be carried out. All study variables will be presented for stent groups and in total, using descriptive statistics in accordance with the nature of the variable. Thus, continuous variables will be described indicating the number of non-missing observations, mean, standard deviation, minimum, first quartile, median, third quartile, and maximum. The categorical variables will be described indicating the number of non-missing observations and the percentages of the different categories.

Realization of the aim of the study will be analyzed by comparing the cumulative incidence of RBO (as a stent dysfunction parameter) in the LAMS cohort versus LAMS-DPS cohort using a Chi-Square test. The magnitude of the effect will be estimated through an incidence ratio and relative risk with 95% confidence interval. The main analysis will be replicated in an adjusted way using a binomial regression model. Age, sex, oncological status, and comorbidities will be taken as adjustment variables.

Safety will also be evaluated by describing the number and type of AE in each study group, and the incidence will be compared using a chi-square test. In addition, the survival of patients will be analyzed according to the two proposed strategies until the end of follow-up, describing the Kaplan-Meyer curves and comparing them using the LogRank test. The level of statistical significance is established at *p* value < 0.05.

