##### Subgroup analysis

The main analysis will also be carried out in the following subgroups:
Age < 65 vs. age > 65.Presence of liver metastasis vs. Absence of liver metastasis.

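### The primary chi-square test ignores the two factors that stratify the randomisation, and the adjusted model does not name liver metastases

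*Protocol article*

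**What the plan says.** Under Randomization and masking, allocation is 1:1 in blocks of four, "stratified by age (< 65 years old/> 65 years old) and by the presence of liver metastases". The reason given for the second factor is: "The assumption is made that liver metastasis may elevate bilirubin and cholestasis parameters without involving bile duct obstruction".

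Under Statistical analysis, the cumulative incidence of RBO is compared between arms with a chi-square test. No stratification is mentioned and no continuity correction is specified. The comparison is then repeated in a binomial regression, for which "Age, sex, oncological status, and comorbidities will be taken as adjustment variables". Age is therefore in the model, though the text does not say whether at the 65-year cut. Liver metastases are not named, and the article does not say what oncological status covers.

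Under Subgroup analysis, the main comparison is repeated by liver metastasis status and by "Age < 65 vs. age > 65". As in the randomisation section, neither age category includes a patient aged exactly 65.

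**The concern.** Stratified allocation balances the arms on the chosen factors. If those factors predict the outcome, the balance reduces the true variability of the difference between arms. A test that ignores the strata still uses the larger, unstratified variance, so it rejects less often than its nominal level and can lose power.

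The protocol gives its own reason to expect a link with the outcome: it stratifies by liver metastases because they can raise cholestasis markers, and a rise in those markers is part of the RBO definition in Table 2. Even so, neither the primary test nor the adjusted model is certain to take the factor into account. It appears by name only as a subgroup split.

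The gap at age 65 is a separate, smaller slip, but it affects a rule that determines allocation.

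**Working it through.** **1. The plan's own sample size.** Inputs from Sample size calculation: 20% versus 1%, 80% power, two-sided 5%. With pooled variance and no continuity correction, the mean proportion is (0.20 + 0.01)/2 = 0.105 and

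n = [1.960 × √(2 × 0.105 × 0.895) + 0.8416 × √(0.20 × 0.80 + 0.01 × 0.99)]² / 0.19² = (0.850 + 0.347)² / 0.0361 = 39.7, so 40 per arm.

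This matches the stated 40 per arm (80 in total), and 80 × 1.05 = 84. A continuity-corrected formula would give 50 per arm, so the plan was sized for an uncorrected chi-square. The formula puts power at 80.3% for 40 per arm. Exact enumeration of the uncorrected chi-square gives 90.9%, because the normal approximation is poor at a 1% rate. That is why the powers below lie near 90%.

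**2. Expected events.** 40 × 0.20 + 40 × 0.01 = 8 + 0.4 = 8.4.

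**3. Unstratified against stratified test.** Each scenario has 200,000 simulated trials with N = 80 and blocks of four within four strata (age × liver metastases). The documents give neither stratum shares nor prognostic strengths. Assumed: 35% with liver metastases, 60% in the older stratum, and the odds ratios (OR) for RBO shown. Both tests are without continuity correction. Each cell shows chi-square / CMH, in percent.

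| OR metastases / OR age | Type I error, 20% in both arms | Power, 20% vs 1% | Power, assumed 30% vs 8% |
|---|---|---|---|
| 1 / 1 | 5.1 / 4.9 | 89.7 / 88.7 | 74.4 / 73.6 |
| 3 / 1.5 | 4.5 / 4.9 | 90.0 / 89.5 | 74.7 / 75.4 |
| 5 / 2 | 4.0 / 4.9 | 90.2 / 90.2 | 75.3 / 77.8 |
| 10 / 3 | 3.0 / 5.0 | 90.8 / 91.6 | 76.4 / 82.0 |

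At the planned rates, stratifying changes power by -1.0 to +0.8 points. At 30% versus 8% it changes power by -0.8 to +5.6 points. A rerun with a different random seed agreed with every cell to within 0.2 points.

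**4. Load on the adjusted model.** Counting one term each for treatment and the four listed covariates gives 8.4/5 = 1.7 events per term. Adding liver metastases gives 8.4/6 = 1.4. Treatment plus the two stratification factors gives 8.4/3 = 2.8, still sparse but the lightest of the three.

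**The case against.** The case for leaving the plan alone has several parts.

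- **No power is lost at the planned rates.** This stands: the table shows at most about 1 point either way.
- **The unstratified test is not invalid.** This stands: it errs on the conservative side, and only if the factors predict RBO, for which the documents give no figure.
- **Oncological status may be meant to include metastases, and covariate definitions can be left to the analysis plan.** This stands in part. The omission alone would be weak, but the primary test itself is fixed as unstratified. The Statistical analysis plan section carries the described analyses forward and requires an addendum for a change on the main variable.
- **The factors are not wholly unused.** True: age is in the regression and both define subgroups. The primary test uses neither.

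Two stronger readings are tempting and unsupported. A reader might infer a large power loss by setting R's default chi-square (72-74% at 20% versus 1%) against a mid-p stratified CMH test (87-88%). Most of that gap comes from the Yates correction, which the protocol does not specify and its sample size does not use. With mid-p tests on both sides, stratifying adds about 1 to 2 points.

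A reader might also infer that liver metastases confound the primary result. Table 2 requires imaging or endoscopic evidence of obstruction as well as the marker rise, so a rise caused by metastases alone does not count as RBO. Stratified allocation also balances the factor between arms in expectation.

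**Conclusion.** The mismatch between design and analysis is real and worth correcting, but its effect is moderate. The primary test is valid and possibly conservative: its type I error falls from about 5% to 4-4.5% with moderate prognostic effects and 3% with very strong ones, while the stratified test stays near 5%. The power effect is about nil at 20% versus 1%, and lies between a 1-point loss and a 6-point gain at 30% versus 8%. The stated sample size is unaffected. These figures rest on the assumed stratum shares and odds ratios. The missing place for age 65 is certain from the text but minor.

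**What to change.** - **Primary comparison:** use a CMH test stratified by the two randomisation factors, with a Mantel-Haenszel risk difference or relative risk and 95% confidence interval. The risk difference is the safer main estimate. At a 1% rate, the chance of no event among 40 patients is 0.99^40 = 67%, and a relative risk of zero has no usual interval.
- **Adjusted regression:** limit it to treatment, age group and liver metastases, rather than adding liver metastases to the present list. State how the model will be fitted if one arm has no events.
- **Age categories:** write them as < 65 versus ≥ 65, or as whichever cut the randomisation list actually uses, in both the randomisation and the subgroup sections. Recruitment began in November 2020, so check how any patient aged exactly 65 was allocated.

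The cost is a short protocol addendum, which the protocol's own rule for the main variable calls for, and matching wording in the analysis plan before the database closes. Both factors are needed at randomisation, so no new data and no extra patients are required.

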#### Definitions

Technical success is defined as successful placement of the stents (LAMS, DPS, or both) between the extrahepatic bile duct and gastrointestinal lumen by endoscopy, endosonography, and, optionally, fluoroscopy.

Clinical success is defined according to the TOKYO criteria as a 50% decrease in or normalization of total serum bilirubin level within 14 days of index procedure (stent placement). For cholangitis without obstructive jaundice (e.g., segmental cholangitis, cholecystitis), success can be defined as cessation of antibiotics or a 50% decrease in or normalization of levels of blood inflammatory markers within 14 days of stent insertion [20].

RBO is defined as a composite endpoint of stent dysfunction (either occlusion or migration). See Table 2 (outcomes) for complete information [20].

**Table 2 Tab2:** Primary and secondary endpoints

**Primary endpoint:** - Rate of recurrent biliary obstruction (RBO) between the two strategies (LAMS with and without coaxial DPS), detected during follow-up. *RBO is associated with a stent dysfunction (an endpoint of either occlusion^a^ or migration^b^). Tokyo criteria - Clinical recurrence (jaundice, fever, suspicious colangitis, pruritus). - Recurrence of cholestasis parameters (Any increase in GGT/ALP or bilirubin from its lowest level post-index procedure). Both WITH evidence of biliary obstruction on imaging (dilation on US/CT/MRI) or endoscopic findings suggesting it ^c^.	
**Secondary endpoints:** - Technical success defined as successful stents (LAMS, DPS, or either) between the extrahepatic biliary duct and the upper gastrointestinal tract determined by endoscopy, endosonography, or fluoroscopy. - Clinical success defined as > 50% decrease in bilirubin at 14 days from stent placement. For cholangitis, clinical success is defined as cessation of antibiotics or normalization of levels of blood inflammatory markers within 14 days of stent placement. - Safety, as defined per the ASGE lexicon/Tokyo criteria for endoscopic AEs and divided into early adverse events (within 14 days of index procedure) and delayed AE (> 14 days). - Additional outcomes: t-RBO, BRI, procedure time, and survival/mortality rates.	

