#### Sample size calculation

The sample size calculation is based on the primary hypothesis of detecting significant differences in the rates of RBO and BRI between the LAMS and LAMS plus DPS groups (assessing for superiority).
Null hypothesis (H0): πLAMS = πLAMS-DPSAlternative hypothesis (H1): πLAMS ≠ πLAMS-DPS

Based on recently published data, we estimate a recurrent biliary obstruction rate of 20% vs. 1% for the LAMS alone vs. LAMS-DPS groups, respectively up during the follow-up period [13, 19, 22]. To achieve a statistical power of 80% with a two-sided type I error of 5%, a total of 80 patients (40 in each arm) is required to reject the null hypothesis. https://www.stat.ubc.ca/~rollin/stats/ssize/b2.html

Considering a 5% dropout rate, a final sample of 84 patients (42 patients in each arm) is needed.

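### The survival log-rank test names no strata although randomisation is stratified by age and liver metastases; stratifying it is a minor, nearly free improvement

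*Protocol article*

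**What the plan says.** Randomization and masking: allocation is 1:1 and "stratified by age (< 65 years old/> 65 years old) and by the presence of liver metastases". The same section adds that "the entire population will be randomized in blocks of four between the two treatment possibilities". The reason given for the metastasis stratum is that "liver metastasis may elevate bilirubin and cholestasis parameters without involving bile duct obstruction". Mortality is not mentioned there.

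Statistical analysis: survival up to the end of follow-up is handled by "describing the Kaplan-Meyer curves and comparing them using the LogRank test". No strata or covariates are attached to this comparison. The primary outcome, recurrent biliary obstruction (RBO), is compared "in the LAMS cohort versus LAMS-DPS cohort using a Chi-Square test" and then repeated in a binomial regression: "Age, sex, oncological status, and comorbidities will be taken as adjustment variables". That adjustment, and the subgroup analyses by age and liver metastases, are tied to the main RBO analysis only.

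Table 2 lists survival near the end of the secondary endpoints: "Additional outcomes: t-RBO, BRI, procedure time, and survival/mortality rates". The Sample size calculation rests on RBO alone. The section headed Statistical analysis plan says that the plan will be finalised before the database is closed and will contain the analyses described and others. That plan is not shown.

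**The concern.** Stratified allocation forces the two arms to be nearly equal in age group and metastasis status. If those factors drive survival, chance imbalance in them no longer contributes to the difference between arms. The variance formula of the plain log-rank test still allows for it. The test statistic then varies less than the standard normal reference assumes, and the test rejects too rarely when there is no effect. Pooling patients of very different risk also pulls the treatment contrast towards the null. Both effects lower power. A log-rank test stratified by the allocation factors removes both.

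At stake is a patient-relevant outcome in a trial of 84 patients, where power for survival is limited in any case. The protocol's Discussion also argues that a confirmed benefit of the added stent would affect survival. Both factors are known at randomisation, so any loss is avoidable without new data.

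**Working it through.** **The plan's own figure.** No event count, hazard ratio (HR) or power is stated for survival. The only calculation is for RBO, from a "recurrent biliary obstruction rate of 20% vs. 1% for the LAMS alone vs. LAMS-DPS groups", 80% power and two-sided 5%. With pooled variance, mean proportion 0.105 and difference 0.19:

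n per arm = [1.96 × √(2 × 0.105 × 0.895) + 0.8416 × √(0.20 × 0.80 + 0.01 × 0.99)]² / 0.19² = (0.850 + 0.347)² / 0.0361 ≈ 39.7, rounded up to 40.

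Power at 40 per arm is 80.3%, and 80 × 1.05 = 84. The stated 80 and 84 reproduce. The survival test does not enter this calculation.

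**The two tests.** At each death j, let g_j be 1 if the death is in the LAMS-DPS arm and 0 otherwise, and let p_j be the share of those at risk who are in that arm.
- Plain: Z = U/√V, with U = Σ(g_j − p_j) and V = Σ p_j(1 − p_j) over all patients.
- Stratified: compute U and V within each of the four strata, add them up, then Z = ΣU/√ΣV.

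**Inputs from the protocol.** 84 patients, 1:1 allocation, two binary stratification factors, blocks of four (taken as blocks within strata), one year of follow-up, two-sided 5%.

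**Assumptions not in the protocol.** Exponential survival with a median of about 8 months, 65% in the older group, 35% with liver metastases, and a treatment HR of 0.5 for the power columns. With equal survival in both arms this gives about 53 to 54 deaths. There were 20,000 simulated trials per row.

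| Assumed HR for death: age, metastases | Variance of plain Z under the null | Type I error, plain / stratified | Power, plain / stratified | Loss (points) |
|---|---|---|---|---|
| 1, 1 | 1.02 | 5.4% / 5.5% | 62.4% / 61.5% | −0.9 |
| 1.2, 1.5 | 0.98 | 4.8% / 5.2% | 62.1% / 62.4% | 0.3 |
| 1.3, 2 | 0.93 | 4.1% / 5.0% | 59.2% / 61.8% | 2.6 |
| 1.5, 3 | 0.85 | 3.3% / 5.3% | 53.7% / 61.7% | 8.0 |
| 2, 4 | 0.74 | 2.3% / 5.1% | 46.8% / 61.0% | 14.2 |

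Simulation error is about √(0.05 × 0.95 / 20,000) = 0.15 points for type I error and √(0.6 × 0.4 / 20,000) = 0.35 points for each power figure.

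**Check on the mechanism.** The type I error should follow from the shrunken variance of Z. At variance 0.846 (row 1.5, 3), 1.96/√0.846 = 2.13, which has a two-sided tail of 3.3%. That matches the simulated figure.

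**Check on the power level.** With no prognostic effect, 42 per arm and median 8 months, the chance of death by 12 months is 1 − 2^(−1.5) = 0.646 in one arm and 1 − 2^(−0.75) = 0.405 in the other. Expected deaths are 42 × (0.646 + 0.405) ≈ 44. The Schoenfeld approximation gives Φ(√(44.2/4) × 0.693 − 1.96) ≈ 63%, close to the simulated 62.4%.

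**A second set of assumptions.** With 40% having metastases, 60% older (HR 1.3), a baseline hazard of 0.09 per month and 4,000 runs, the results are:
- Metastasis HR 2: type I error 4.1% plain against 5.3% stratified; power 71% against 74% (0.738 − 0.711 = 2.7 points).
- Metastasis HR 3: type I error 2.9% against 5.1%; power 64% against 73% (0.734 − 0.641 = 9.3 points).

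Absolute power is higher because the assumed hazards are higher. The direction and the size of the loss agree.

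**The case against.** The strongest objection is that the protocol never says "unstratified". A stratified log-rank test is still a log-rank test, and whether the strata are carried is a detail that an analysis plan often settles. This stands in part: a reader might infer that the protocol has deliberately rejected stratification, and the text does not support that. But the test is named without strata, and nothing else in the article brings the allocation factors into the survival comparison. A plain reading gives the ordinary test. The point is therefore a better specification of a stated analysis, not a contradiction.

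A second objection is that the harm depends on prognostic effects that the protocol does not give. This stands. The stated reason for the metastasis stratum concerns bilirubin, not death. A reader might infer that the survival p-value will certainly be too large; that follows only if the strata predict survival. With the weakest prognostic effects in the table there is practically no loss.

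A third objection is that an HR of 0.5 for death is generous and that smaller effects would be missed with either test. This also stands. Under the same no-prognosis assumptions, an HR of 0.7 gives 42 × (0.646 + 0.517) ≈ 49 deaths and Φ(√(48.9/4) × 0.357 − 1.96) ≈ 24% power. The choice of test would then seldom change a conclusion.

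Finally, the plain test corresponds to the marginal Kaplan-Meier curves, while the stratified test addresses a within-stratum contrast. Both are accepted. This is a reason to keep the curves as planned, but it does not outweigh the gain from analysing as randomised.

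**Conclusion.** The point holds as a minor, nearly free improvement. Randomisation is stratified by age and liver metastases, and the survival log-rank test is named without them. If the factors predict survival, the plain test is conservative and less powerful. At a treatment HR of 0.5 the loss is about 0 points with weak strata, 2 to 3 points at a metastasis HR of 2 and 8 to 9 points at an HR of 3. These figures rest on assumed survival, stratum sizes and prognostic effects, none of which the protocol states.

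Three limits apply. Leaving the strata out does not inflate type I error, so no false claim of a survival benefit arises from it. Survival is an additional outcome with no power attached. The primary chi-square test and the sample size of 84 are unaffected, so it would be wrong to read this as a weakness of the trial's main conclusion. No test is named for time to RBO, so nothing stated about that outcome needs correcting here.

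**What to change.** State in the Statistical analysis section, or in the analysis plan before the database is closed, that survival is compared with a log-rank test stratified by age group and liver metastases exactly as used for allocation. Add that the hazard ratio and its 95% confidence interval come from a Cox model stratified in the same way. Keep the Kaplan-Meier curves by arm as planned. Take the strata from the randomisation record; the text defines the age groups as below and above 65 and does not place a patient aged exactly 65.

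The cost is one sentence and no new data. The downside is about 1 point of power if the strata are not prognostic (62.4% against 61.5% in the table). Four strata are workable at this size: under the assumed proportions the smallest expects 84 × 0.35 × 0.35 ≈ 10 patients, and the stratified test's type I error stayed between 5.0% and 5.5% in every row.

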##### Subgroup analysis

The main analysis will also be carried out in the following subgroups:
Age < 65 vs. age > 65.Presence of liver metastasis vs. Absence of liver metastasis.

#### Statistical analysis plan

The statistical analysis plan will be finalized before the close of the database. This plan will include all the analyses described and others, mainly on the sensitivity of the results and the management of the missing data. If there is some deviation in the plan of statistical analysis regarding the main variable, an addendum to the protocol will be made. No changes will be made to the original analysis plan once the database is closed.

No interim analysis is planned given the short accrual time, relatively small sample size, and short follow-up period.

#### Other considerations

##### Rescue by e-BRI and cross-over

Depending on the initial endoscopic treatment carried out, in case of stent dysfunction or RBO, cross-over rescue treatment may be considered when the initial per-protocol strategy fails:
In LAMS cohort: adding a co-axial DPS through LAMS.In LAMS-DPS cohort: removing DPS and leaving LAMS or adding another coaxial stent, either fully-covered self-expandable metal stent or another DPS.

These potential cross-over options are considered in the e-BRI, described in a previous section (see definitions). In all these situations, the follow-up will be maintained until the end of the study in accordance with the protocol. Alternatively, if an endoscopic technique is not possible, other options (such as radiological intervention) will be offered.

